### Structural readiness to implement

When a health system is preparing to implement a new intervention or to change standard practice, effective implementation of the change may be influenced by the degree to which stakeholders identify the system as “ready” to implement the change or practice. Within DeWorm3, readiness implies that individuals feel empowered as members of the health system to contribute to the new interventions, they are confident in the flexibility and responsiveness of the system to adapt to the change, they are not threatened by the change, and they believe intervention is appropriate for achieving desired outcomes. With the repurposing of community-wide LF MDA platforms for STH transmission interruption and a transition from targeted to community-wide MDA, there will be a considerable need for systems adaptation and a multi-level and multi-faceted assessment of the government and its partners’ readiness to implement [22].

It is important to understand the factors that drive health system readiness to implement novel interventions such as community-wide MDA for STH both in order to contextualize observed trial outputs and outcomes as well as to provide evidence-based guidance in other settings regarding health system factors that should be in place prior to implementation [23]. Drawing from organizational readiness for change theory, DeWorm3 has developed a structural readiness assessment survey tool [24]. At baseline, the tool will be used to identify needs or conditions that can be targeted for effective change management. At study endline, the readiness tool will be used in a prognostic manner to evaluate health system readiness to sustain or scale-up the intervention [24].

#### Data collection and analysis

The readiness survey instrument aims to capture an individual’s perception of the structural readiness of the health system as well as the downstream phenomena of psychological readiness. Readiness indicators fall into six domains, including: the policy environment, leadership structure, financial resources, material resources, technical capacity, and community delivery infrastructure. Survey questions within each domain are intended to assess the health system’s readiness to launch the new community-wide MDA intervention, deliver community-based public health programs, and function collaboratively. Knowledge assessment questions are used to score a survey participants knowledge of a specific domain, and weight their responses to domain questions accordingly.

The sampling frame for survey participants is defined by the network of individuals identified during baseline stakeholder mapping and updated over time. Participants will be selected using restricted random selection to ensure participation from at least 10% of individuals in each stakeholder group (i.e. national level government staff, CDDs, external partners, etc.), attain sufficient representation from each stakeholder group, and variation across stakeholder groups. Random selection of participants at the local level (health center staff and CDDs) will be restricted to five randomly selected clusters. Surveys will be either self-administered by literate participants or administered in-person by trained study personnel in the local language.

Mean readiness scores and standard deviations will be calculated by site and stakeholder group. We will assess concordance between indicator scores within sites using analysis of variance (ANOVA) models to understand variation in scores amongst and between stakeholder groups.

### Process mapping

Process mapping is a systems analysis approach to identifying the flow of inputs required to achieve optimal outputs, such as high MDA treatment coverage. Process mapping generates a systems-wide view of complex, interdependent components that can contribute to effective MDA programs with high coverage. Process mapping also helps build a shared understanding of how work is carried out and promotes common organizational goals, while simultaneously generating information regarding what aspects of the intervention are adaptable across settings and which are key determinants of intervention uptake.

DeWorm3 will use two process mapping methods. The first is in-depth process mapping, which will take place annually in six randomly selected clusters over the duration of the trial. The second is routine workflow mapping, which will take place in each cluster during each round of MDA. The in-depth process mapping will help identify all activities that must take place in school or community-based MDA programs, *ideal* activity levels for achieving optimized outputs, *actual* activity achievements, and the discrepancy between ideal and actualized activities. Routine workflow tracking will provide information regarding key activity performance in each cluster, and how different activities may or may not be tied to reaching treatment coverage targets. Both of these strategies will identify contextually-relevant modifiable bottlenecks that may be addressed to improve the intervention delivery process and to achieve key intervention outputs.

#### Data collection and analysis

At baseline, implementation science teams in six different clusters per site will engage in guided in-depth process mapping activities. Clusters will be selected based on site-specific indications of capacity. In some sites, this may be historical targeted STH coverage, LF coverage, or immunization coverage. We will use restricted randomization to select two DeWorm3 intervention clusters with high baseline capacity, two intervention clusters with low baseline capacity, one control cluster with high baseline capacity, and one control cluster with low baseline capacity. By including clusters with heterogeneous baseline capacity indications, we augment our ability to observe how the delivery environment responds to or evolves in the context of the DeWorm3 intervention. IS teams in each selected cluster will identify all of the activities and the flow of activities necessary for delivering school-based or community-wide MDA. Ideal metrics and timelines will be identified for each activity. For example, for the activity of sensitization of village leaders, the ideal metric may be that 80% of village headmen with phones are called about an upcoming MDA campaign and the ideal timeline may be one week in advance of drug delivery.

Activity tracking will be ongoing. Once per year, following MDA in both trial arms, selected clusters will record how each mapped activity actually occurred, including the metrics achieved and the relevant time points. This will facilitate analysis of the number of activities that did not meet ideal benchmarks, and if these activities act as bottlenecks to implementing subsequent “downstream” activities. T-tests will be performed to identify if there are changes in the number of activities that do not meet targets within clusters across study years, if certain activity targets are consistently associated with high or low coverage, as well as if there are differences in the number of bottlenecks identified in clusters achieving high or low coverage.

A routine process mapping worksheet will be conducted in all intervention and control clusters during each round of MDA. These worksheets detail activities that must take place in the effective delivery of the intervention. Routine mapping provides opportunities to optimize the intervention in real-time, to systematically measure study inputs and processes, to promote the replicability of the trial, and to identify trial components that may be easily modified or adapted with minimal effects on MDA coverage. Observations from the in-depth process mapping activities will also be used to refine the routine workflow trackers in order to build a useful monitoring tool that may be applicable in other settings.

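### The coverage comparison tests raw bottleneck counts across clusters whose activity lists may differ in length; a proportion within programme type would remove that distortion

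*Protocol article*

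**What the plan says.** The relevant text is in the protocol article, Methods, Process mapping, under Data collection and analysis.

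- **Sample.** At baseline, "implementation science teams in six different clusters per site will engage in guided in-depth process mapping activities". Restricted randomisation selects "two DeWorm3 intervention clusters with high baseline capacity", two intervention clusters with low capacity, and one high-capacity and one low-capacity control cluster.
- **Activity lists.** "IS teams in each selected cluster will identify all of the activities and the flow of activities necessary for delivering school-based or community-wide MDA". An ideal metric and timeline are then set for each activity.
- **Outcome.** Once a year the selected clusters record what happened to each mapped activity, to allow "analysis of the number of activities that did not meet ideal benchmarks" and to see whether missed activities hold up later ones.
- **Tests.** "T-tests will be performed to identify if there are changes in the number of activities that do not meet targets"; the sentence goes on to place this comparison within clusters, from one study year to another. It also applies t-tests to whether particular targets go with high or low coverage, and to "differences in the number of bottlenecks identified in clusters achieving high or low coverage".

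The Process mapping section also describes a second data source, "routine workflow mapping, which will take place in each cluster during each round of MDA". Its stated purpose includes showing how activities relate to reaching coverage targets.

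**The concern.** A count of bottlenecks compares performance fairly only if every cluster had the same number of activities that could fail. Here the lists are drawn up in each selected cluster, for one of two delivery programmes. School-based and community-wide MDA need not involve the same number of steps, and two teams mapping the same programme need not divide it equally finely. A cluster with a longer list will show more bottlenecks at the same rate of failure.

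The comparison by coverage is the one exposed. It sets clusters from both programmes against each other, and the article gives no denominator. If control clusters tend to fall in one coverage group, the test partly compares programme types. These analyses are meant to find modifiable bottlenecks and to inform delivery and scale-up, so an effect of list length could be reported as a correlate of coverage.

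**Working it through.** The article gives no sample size, power, significance level or list length for this analysis, so there is no stated figure to reproduce. The cluster numbers agree: 2 + 2 + 1 + 1 = 6 per site, four intervention and two control.

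**Assumptions (not in the documents).** Intervention lists have 24 activities and control lists 12. Each activity is a bottleneck with probability 0.30 in every cluster, independently, so true performance is equal. Coverage groups are 3 v 3 per site. Pooling is over three sites, one for each country named in the Introduction. Tests are two-sided at 5%, by simulation.

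**Step 1: expected counts.**
- Intervention cluster: 0.30 × 24 = 7.2.
- Control cluster: 0.30 × 12 = 3.6.
- Both controls in the high-coverage group: high-group mean (3.6 + 3.6 + 7.2)/3 = 4.8 and low-group mean 7.2. The difference is 2.4 bottlenecks with no difference in performance.
- One control in each group: both means are (3.6 + 7.2 + 7.2)/3 = 6.0. The difference is 0.

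**Step 2: how often the t-test rejects when performance is equal.**

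| Lists (intervention v control) | Controls | Counts, one site (3 v 3) | Counts, three sites (9 v 9) |
|---|---|---|---|
| 24 v 12 | both high coverage | about 12% | about 52% |
| 24 v 18 | both high coverage | about 7% | about 18% |
| 24 v 20 | both high coverage | about 6% | about 11% |
| 24 v 12 | one in each group | about 1% | about 1% |

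Placing both controls in the low-coverage group gives the same figures as the first three rows, with the sign reversed. Proportions give about 5% in every row (4.4% to 5.4%).

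A second check lets list length follow coverage group completely, whatever the arm. With 20 v 30 activities the mean counts are 6 v 9, and the count t-test rejects in 23% (3 v 3) or 74% (9 v 9). With 20 v 25 it is 9% and 28%. Proportions again stay at about 5%.

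**Step 3: what six clusters can detect.** From the noncentral t distribution at 80% power, with noncentrality d / √(1/n₁ + 1/n₂), the smallest detectable difference is 3.1 SD for 3 v 3, 3.3 SD for 2 v 4, and 1.4 SD for 9 v 9.

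**Step 4: repeated years in the coverage comparison.** The article does not say how yearly records enter this test. If three years from six clusters were treated as 18 independent values (9 v 9), the false-positive rate would be 13%, 19% and 25% at a within-cluster correlation of 0.3, 0.5 and 0.7. One mean per cluster (3 v 3) keeps it at about 5%.

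**Step 5: the comparison across years.** With unequal lists that stay fixed (20 to 40 activities), a paired t-test rejects in 4.8%. The denominator cancels within the cluster, so there is no artefact.

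**The case against.** The strongest reply is that the large figure is a worst case. It needs lists in a 2:1 ratio, both controls in the same coverage group at every site, and pooling over sites, and the article states none of these. The design works against the second condition: one control per site has high and one has low baseline capacity, and capacity may be measured by historical coverage. With an even split the count test is conservative. The mapping is also guided, so some standardisation of lists is plausible. In addition, the simulation assumes independent failures. The article expects missed activities to block later ones, which would add noise and lower these rejection rates. All of this stands. It limits the size of the problem, but it does not give the counts a common denominator, and coverage achieved in the trial need not follow baseline capacity.

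A reader might also infer that the plan ignores repeated measures, or that differences between years could be artefacts. The documents do not support either reading. The year comparison is described as within clusters, which fits a paired test. The same mapped activities are recorded each year, so the list length is constant as the text reads. Even an unpaired test would be conservative under positive within-cluster correlation (2.5%, 1.3% and 0.4% false positives at 0.3, 0.5 and 0.7). Whether tests are paired, how three years are combined, and which test is used on the routine worksheets are details that an article may leave to the full protocol or analysis plan.

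**Conclusion.** The point holds for the coverage comparison only. The plan fixes t-tests on the raw number of bottlenecks between clusters whose lists may differ in length and serve two programmes. Equal performance can then give different counts if list length is related to coverage or arm. The size is unknown because no list length is documented. Under the assumptions above, false positives run from none in excess (even split of controls) to about 12% per site and about 52% pooled (2:1 lists, controls all in one coverage group). Proportions stay at about 5% throughout. Separately, a 3 v 3 comparison can detect only about 3.1 SD, so a null result at one site would say almost nothing. Severity is modest: this is exploratory process research with no confirmatory claim.

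**What to change.** 1. For the coverage comparison, replace the count with the proportion of mapped activities that miss target or act as bottlenecks.
2. Compare within programme type, or adjust for arm.
3. Keep the cluster as the unit, with one summary per cluster or a model with a cluster effect, so that yearly records are not counted as independent. A model should also allow for dependence between activities in the same cluster and year, since one failure may cause the next.
4. Describe the six-cluster comparison within a site as descriptive. Base associations between activities and coverage on the routine worksheets, which are already planned for all clusters at every round.

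The cost is a few sentences of analysis text and no new data collection. Two small downsides follow. Activities specific to one cluster would be reported descriptively. With only two control clusters per site, a within-programme comparison on the control side is at most 1 v 1 and cannot be tested at site level.

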Clinical trials that incorporate implementation or operational research questions are referred to as hybrid studies [5]. The DeWorm3 Project was launched in 2016 as a series of large hybrid trials in Benin, Malawi, and India. The purpose of these trials is to test the feasibility of interrupting the transmission of soil transmitted helminths (STH) using expanded chemotherapeutic approaches while concurrently generating information on the opportunities, challenges, and best-practices for delivering novel STH transmission interruption programs. DeWorm3 aims to preemptively bridge the “know-do” gap by using IS methods to speed the evidence translation process needed to inform STH elimination guidelines, public health practice, and policies and operational plans. By embedding rigorous IS methods within DeWorm3, we aim to (1) describe the implementation environment that contextualizes clinical research findings, and (2) if interventions are found to be efficacious, to generate evidence regarding effective strategies for promoting and scaling-up the interventions to interrupt transmission. This research builds and expands upon prior NTD implementation research from Uganda [6, 7] and Kenya [8, 9] including the ongoing work by the Tumikia project, another randomized trial evaluating the impact of intensified deworming on hookworm transmission [10].

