At midline and endline, qualitative research at the cluster level will take place in four randomly selected clusters per site: two high coverage clusters (80–100% average treatment coverage in year 1) and two low/moderate coverage clusters (<80% average treatment coverage in year 1). CFIR constructs will provide a framework for understanding why the DeWorm3 intervention may exhibit differential effectiveness across settings, correlates of high coverage, and opportunities to optimize the intervention moving forward. Following thematic coding, two independent analysts will assign scores to data at a cluster level to distinguish CFIR constructs that are missing too much data (M), do not distinguish between coverage levels (0), weakly (+1/-1), or strongly (+2/-2) distinguish coverage levels. The ratings reflect the positive or negative influence (valence) and strength of each construct on influencing implementation [18]. These relationships will be evaluated using chi-square tests. Findings will be synthesized to develop recommendations for best practices and highlight barriers and facilitators of implementation in high and low coverage sites.

Quality control will be ensured through a process of (1) random one minute spot checks of each transcribed audio file at a site level, (2) coding review and confirmation of 10% of coded transcripts from each site at the central DeWorm3 level, and (3) coding review and confirmation of 5% of coded transcripts between sites (i.e. circular quality assurance).

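### Process mapping: grouping cluster coverage into high and low for the t-tests discards information in a very small sample; a minor and nearly costless improvement is to keep coverage as a percentage

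*Protocol article*

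**What the plan says.** All references are to the protocol article, Methods.

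- **Sample.** Under Process mapping, Data collection and analysis, "implementation science teams in six different clusters per site will engage in guided in-depth process mapping activities". Besides two intervention clusters with high baseline capacity, these are "two intervention clusters with low baseline capacity, one control cluster with high baseline capacity, and one control cluster with low baseline capacity". Selection is therefore on baseline capacity and arm.
- **Tests.** The same section names t-tests for three questions. The first does not involve coverage: "T-tests will be performed to identify if there are changes in the number of activities that do not meet targets within clusters across study years". The other two do: "if certain activity targets are consistently associated with high or low coverage", and "if there are differences in the number of bottlenecks identified in clusters achieving high or low coverage".
- **Cut-point.** This section gives none. A numerical boundary appears only under Qualitative research, where midline and endline clusters are sampled as "two high coverage clusters (80–100% average treatment coverage in year 1) and two low/moderate coverage clusters (<80% average treatment coverage in year 1". That text also shows that coverage is held as a percentage.
- **Not stated for these tests.** The article gives no significance level, power, effect size or standard deviation, and does not say whether sites are pooled.

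**The concern.** In the qualitative work the clusters are sampled by coverage level, so a high/low contrast follows from the design. In process mapping nothing in the sampling depends on achieved coverage. Cutting the percentage into two groups there ignores all differences within each group and treats clusters just either side of the cut as opposites. Without a stated cut, the grouping can also be settled after the data are seen.

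The purpose is to find which activities and bottlenecks go with good or poor coverage. With six clusters per site there is little information to begin with, and in some sites nearly all clusters may fall on one side of the cut. The two-group test is then uninformative or impossible, although the coverages still differ.

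**Working it through.** The plan has no figure of its own to reproduce, so the check asks what the split costs under stated assumptions.

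**Inputs from the article.** Six in-depth clusters per site, four intervention and two control. The project is described thus: "The DeWorm3 Project was launched in 2016 as a series of large hybrid trials in Benin, Malawi, and India". One site per country gives 3 × 6 = 18 clusters if pooled.

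**Assumptions.** Pooling for n = 18; two-sided 5% level; one record per cluster; bottleneck count and coverage bivariate normal with correlation ρ; independent clusters.

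**Large-sample check.** A median split keeps 2/π = 0.637 of the information, so the non-centrality is multiplied by √(2/π) = 0.798.

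- From 80% power: Φ[(1.960 + 0.842) × 0.798 − 1.960] = Φ(0.276) = 61%.
- From 90% power: Φ[(1.960 + 1.282) × 0.798 − 1.960] = Φ(0.627) = 73%.

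**Small-sample simulation (40,000 runs per setting).** The test of the correlation, t = r√(n−2)/√(1−r²) on n−2 df, is compared with the two-sample t-test after splitting coverage at its median.

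| n | ρ | Continuous | Median split | Loss (points) |
|---|---|---|---|---|
| 18 | 0.3 | 23.1% | 15.5% | 7.6 |
| 18 | 0.4 | 39.2% | 24.7% | 14.4 |
| 18 | 0.5 | 59.1% | 38.3% | 20.8 |
| 18 | 0.6 | 79.0% | 54.5% | 24.5 |
| 18 | 0.7 | 93.0% | 72.7% | 20.3 |
| 18 | 0.8 | 99.1% | 89.8% | 9.3 |
| 6 | 0.3 | 8.4% | 6.8% | 1.6 |
| 6 | 0.5 | 17.0% | 11.0% | 5.9 |
| 6 | 0.6 | 25.0% | 14.1% | 10.9 |
| 6 | 0.7 | 36.7% | 18.1% | 18.6 |
| 6 | 0.8 | 55.2% | 24.3% | 30.9 |

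With an uneven fixed cut that places 75% of clusters in the high group, the losses at n = 18 are larger: 26.4, 32.7 and 30.2 points at ρ = 0.5, 0.6 and 0.7.

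**The recommended model.** A regression with site and arm terms spends degrees of freedom, so it was simulated separately, with ρ as the partial correlation. At n = 18 its power is about 50%, 70% and 87% at ρ = 0.5, 0.6 and 0.7. Against the unadjusted median-split t-test (38%, 55%, 73%) the gain is 50 − 38 = 12, 70 − 55 = 15 and 87 − 73 = 14 points. Within one site, with an arm term only, power is about 13%, 18% and 27%.

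**Unusable splits at n = 6.** Let p be the chance that a cluster falls on a given side of the cut. The probability that fewer than two clusters lie on one side is P(X ≤ 1) + P(X ≥ 5), with X binomial(6, p).

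- p = 0.5: (1 + 6 + 6 + 1)/64 = 22%.
- p = 0.3: 0.118 + 0.303 + 0.010 + 0.001 = 43%.
- One side entirely empty at p = 0.25: 0.75⁶ + 0.25⁶ = 18%.

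**The case against.** Several points against the concern have force.

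- **A single figure for the loss.** A reader might infer that the split costs some 15 to 25 points of power in each six-cluster site. The documents do not support that: they give no correlation, level or pooling rule. That range fits roughly 18 pooled clusters at moderate to strong correlation. At n = 6 the loss runs from about 1 point to more than 30.
- **The 80% boundary.** It is tempting to carry it over and say that clusters at 79% and 40% count as alike. The boundary belongs to the qualitative sampling and is defined on year-1 coverage; the process-mapping text does not adopt it. A condensed article may leave a cut-point to the full plan. The point is therefore that grouping has been chosen, not that the cut is missing or wrong.
- **A mismatched test.** For activity targets one might infer a comparison of two binary variables, which a t-test does not suit. That is only one reading. Mean coverage compared by target met or not met, or achieved activity metrics compared by coverage group, would each suit a t-test.
- **Counts of missed activities.** These are tested across study years, not against coverage, so the criticism does not reach that test.
- **Repeated years and other data.** Activities are recorded annually, so absolute power under one record per cluster does not describe the real dataset. Routine worksheets from every cluster also exist, and it is of these that the article says they will show "how different activities may or may not be tied to reaching treatment coverage targets".
- **Weight.** This is exploratory process research and feeds no trial endpoint.

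These points limit the size and reach of the concern. They do not remove the stated comparison of bottleneck counts between high- and low-coverage clusters, nor the advantage of not grouping.

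**Conclusion.** The point holds as a minor improvement. The article fixes a two-group use of coverage in a sample that was not drawn on coverage, and splitting lost power in every setting checked that was not already at its ceiling.

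The size is conditional on a two-sided 5% level, normality, independent clusters, one record per cluster and a median split. For 18 pooled clusters the loss is about 14 to 25 points at correlations of 0.4 to 0.7, and smaller outside that range. For six clusters in one site it is about 1 to 6 points at correlations of 0.2 to 0.5 and about 19 at 0.7. Power there is poor with either analysis, so continuous coverage does not rescue a per-site test; most of the benefit comes with pooling. The risk of a lopsided split within a site, 22% to 43%, needs only the binomial assumption and a cut between 50:50 and 30:70.

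**What to change.** In Process mapping, Data collection and analysis, replace the two coverage comparisons as follows:

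1. Relate the number of bottlenecks to coverage as a continuous percentage, by regression pooled over sites with site and arm terms and with allowance for repeated years within a cluster.
2. For each activity, compare mean coverage between clusters that met and did not meet the target.
3. Keep the high/low grouping for descriptive display only.

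The t-test of missed-activity counts across years is not affected by this point.

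The cost is a change of analysis wording. The coverage percentages and activity records are already planned, and no further clusters are needed. The downsides are a less simple presentation than a two-group contrast and a few degrees of freedom spent on site and arm, which the 12 to 15 point gain above already takes into account.
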